|  | **Multiple (≥2) metformin scripts filled (N=637)** | **Metformin unexposed**  **N= 2,672** | **Crude RR**  **(95% CI)** | **Inverse probability weighted RR (95% CI)** |
| --- | --- | --- | --- | --- |
| Hypertensive disorders of pregnancy | 43 (6.8) | 209 (7.8) | 0.86 (0.63-1.18) | 0.96 (0.61-1.49) |
| Preeclampsia | 18 (2.8) | 77 (2.9) | 0.98 (0.59-1.63) | 0.96 (0.47-1.95) |
| Preterm preeclampsia <37/40 | 4 (0.6) | 30 (1.1) | 0.47 (0.16-1.39) | 0.56 (0.18-1.73) |
| Pregnancy-induced hypertension | 25 (4.0) | 132 (5.1) | 0.79 (0.52-1.21) | 0.96 (0.53-1.75) |

**Additional File 1: Analysis plan for investigating associations between metformin use in pregnancy and preeclampsia among women with diabetes**

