**Research question**

Among women with diabetes, is metformin associated with a reduced likelihood of preeclampsia?

Main analysis

Overview

P–Nulliparous diabetic (gestational diabetes or Type II diabetes) women with a birth recorded in the Scottish maternity and neonatal birth record between 2009 and 2018

I–Prescription of metformin during pregnancy

C–No prescription of metformin during pregnancy

O–Hypertensive disorders of pregnancy

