**Exposure**

Maternal metformin use during pregnancy will be identified through the Scottish National Prescribing Information System (PIS), which has been linked with the Scottish Morbidity Records. Metformin use will be further categorised as use ever, 0 – 12 weeks, 13 – 27 weeks, and 28 weeks onward. Metformin exposure will be assessed for timing, with only prescription prior to preeclampsia diagnosis included.

1. **Primary outcomes:**

Diagnosis of preeclampsia identified by codes O11, O14 and O15 according to the International Classification of Disease Tenth Revision.

Preeclampsia will be further classified by stratifying according to gestational age at birth; <37 weeks and <34 weeks.

Secondary outcomes:

- Gestational hypertension ICD-O13
- Neonatal birthweight: small for gestational age at birth or large for gestational age at birth (defined according to **1)** < or > 2 SD; adjusted for gestational age and offspring sex or **2)** birthweight centile calculated using GROW charts; <10^th^ percentile for SGA and >90^th^ percentile for LGA) (binary)
- Macrosomia; birthweight >4500g (binary)
- Neonatal intensive care unit admission (obtained via neonatal indicator variable)
- Major congenital abnormality (binary)
- Congenital renal anomaly (binary)
- Perinatal death (binary)
- Preterm birth

1. **Additional analyses:**

- Metformin exposure for any indication, compared to the total unexposed population (whether or not they were diagnosed with diabetes)
- It is anticipated that most women requiring metformin in pregnancy will have been prescribed this in the context of Gestational Diabetes or Type II diabetes. The main analysis has therefore been limited to diabetic women, to eliminate diabetes as a confounder
- By number of scripts filled for metformin (possibly reflects compliance)
- By dose, categorised as 1g and >1g

1. **Outline of statistical analysis**
   1. Descriptive analysis

Summary statistics of baseline characteristics of patients will be presented with mean (SD) used to describe normally distributed continuous variables, median (IQR) for skewed continuous variables, and n (%) for categorical variables. Univariate analyses will be performed for each of the variables of interest to be included in the model.

Population characteristics to be described for:

a) Overall cohort

b) Metformin exposed vs non-exposed cohort

| Characteristic | Descriptor | Total population | Metformin exposed | Metformin unexposed |

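### Metformin is defined by scripts filled during pregnancy but analysed as a fixed group, so risk ratios fall below 1 with no effect, chiefly for two or more scripts and for preterm preeclampsia

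*SAP*

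**What the plan says.** The Research question section sets the contrast as "I–Prescription of metformin during pregnancy" against "C–No prescription of metformin during pregnancy". The Exposure section adds a timing rule, "Metformin exposure will be assessed for timing, with only prescription prior to preeclampsia diagnosis included", and subdivides exposure: "Metformin use will be further categorised as use ever, 0 – 12 weeks, 13 – 27 weeks, and 28 weeks onward". Under Primary outcomes the preterm strata are set by "Preeclampsia will be further classified by stratifying according to gestational age at birth; <37 weeks and <34 weeks", and preterm birth is a secondary outcome. An additional analysis is planned "By number of scripts filled for metformin (possibly reflects compliance)", and Table S4 reports women with two or more scripts against unexposed women.

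The Outcome analysis section puts this exposure into a logistic propensity model and estimates effects by inverse probability weighting, regression adjustment or both. No section gives an index date for unexposed women, a landmark, a time-varying exposure or a split of time at risk. The SAP also does not say whether a woman first dispensed metformin after her preeclampsia diagnosis is unexposed or excluded.

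**The concern.** Exposure becomes known only as pregnancy advances, yet it is analysed as if known at the start. To be exposed, a woman must reach her script undelivered and without preeclampsia. A woman who develops preeclampsia and delivers before any script falls in the comparator, on any reading of the SAP. The exposed group is thus guaranteed event-free time that the comparator is not.

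The cohort includes gestational diabetes and the SAP has a window from 28 weeks onward, so some use is expected at gestations when preeclampsia can already have occurred. A second script needs still more event-free time. Early-onset cases are the most likely to precede a script. The distortion should therefore be greatest for the script-count analysis and the <37 and <34 week strata, and it favours the hypothesis that metformin reduces preeclampsia. A script-count gradient could pass for dose-response. The listed covariates are maternal characteristics, so neither the weights nor the balance and overlap checks would correct or reveal it.

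**Working it through.** **1. Table S4 reproduced.** RR = (a/n1)/(b/n0), with SE of log RR = √(1/a − 1/n1 + 1/b − 1/n0).

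- Preeclampsia: (18/637)/(77/2,672) = 0.98 (0.59–1.63), as stated.
- Preterm preeclampsia: (4/637)/(30/2,672) = 0.56 (0.20–1.58). The stated crude value, 0.47 (0.16–1.39), does not follow from these counts, which is a separate matter. The stated weighted value is 0.56 (0.18–1.73).

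**2. The bias in closed form, with no effect and a rare outcome.** Let s be the share of women who would fill a script if pregnancy ran on. Let q be the share of cases among them whose event comes before the first script, and q2 the share whose event comes before the second.

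- Any script, with those cases counted as unexposed: RR ≈ (1 − q)/(1 + sq/(1 − s)).
- Any script, with those women excluded: RR ≈ 1 − q, still below 1.
- Two or more scripts: RR ≈ (1 − q2)/(1 + sq/(1 − s)).

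From Table S4 (unexposed): risk 77/2,672 = 2.88% and preterm share 30/77 = 0.39. Assumed: s = 0.20 (637/3,309 = 0.19 had two or more scripts); preterm events uniform over weeks 28–37 and term events over weeks 37–40; early users start at week 8; scripts are 4 weeks apart.

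*Late starts (10% early, the rest uniform over weeks 26–36).* For late starters, the chance that a preterm event precedes the script is (1/9)∫₂₈³⁶(36 − t)/10 dt = 3.2/9 = 0.356, so q = 0.9 × 0.356 = 0.32.

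- Preterm: 0.68/(1 + 0.25 × 0.32) = 0.68/1.08 = 0.63.
- All preeclampsia: q = 0.32 × 0.39 = 0.125, giving 0.875/1.031 = 0.85.
- Two or more scripts, preterm: q2 = 0.9 × (2 + 4.55)/9 = 0.655, giving 0.345/1.08 = 0.32.

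With no early users and s = 0.25 to 0.30, q = 0.356 and the any-script values become 0.58 to 0.56 (preterm) and 0.82 to 0.81 (all).

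*Earlier starts (50% early, the rest uniform over weeks 26–32).* q = 0.5 × (16/12)/9 = 0.074.

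- Preterm: 0.926/1.0185 = 0.91.
- All preeclampsia: q = 0.029, giving 0.96.
- Two or more scripts, preterm: q2 = 0.5 × 5/9 = 0.278, giving 0.722/1.0185 = 0.71.

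Simulation on the same assumptions gave 0.85–0.96 (all) and 0.63–0.91 (preterm) for any script, and 0.68–0.89 and 0.34–0.71 for two or more.

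**3. A second simulation, with starts tied to diabetes diagnosis.** True RR = 1 and 8 million pregnancies per scenario. From Table S4: risk 95/3,309 and preterm share 34/95. Assumed: 25% would-be users; second script 4 weeks after the first; preeclampsia diagnosed on average 1 week before birth unless stated; 8% preterm birth in non-cases. Women first dispensed after diagnosis are counted as unexposed.

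| Start pattern | Any script: all / <37 wk | ≥2 scripts: all / <37 wk |
|---|---|---|
| All by week 12 | 1.00 / 1.00 | 1.00 / 1.00 |
| Diabetes diagnosed wk 24–28, script 0–2 wk later | 0.98 / 0.93 | 0.89 / 0.68 |
| Diagnosed wk 24–30, script 1–4 wk later | 0.93 / 0.80 | 0.78 / 0.39 |
| As above, 20% early starters | 0.94 / 0.84 | 0.82 / 0.52 |
| Diagnosed wk 24–32, script 1–6 wk later | 0.85 / 0.59 | 0.65 / 0.25 |
| As above, preeclampsia diagnosed 2 wk before birth | 0.77 / 0.47 | 0.53 / 0.17 |

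If would-be starters with preeclampsia before their script are excluded instead, the any-script values in the scenarios with starts after diabetes diagnosis are 0.82–0.98 (all) and 0.54–0.95 (preterm).

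**4. Does the remedy work?** With a landmark at week 28 or 32, women undelivered and event-free at that point, and exposure fixed by then, the same data give 0.99–1.01 for all preeclampsia and 0.98–1.06 for preterm preeclampsia.

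**The case against.** Five points can fairly be made for the plan.

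- **The timing rule is sound in purpose.** It stops metformin dispensed after diagnosis from counting as exposure. That stands. The fault lies in joining the rule to a fixed group, and deleting the rule would not help.
- **The SAP does not say that early cases move into the comparator.** A reader might infer that every woman first dispensed after diagnosis becomes an unexposed case. The text does not support this: the comparator is defined by no prescription in pregnancy, so excluding her is at least as literal a reading. Exclusion shrinks the bias but does not remove it.
- **The main contrast may be little affected.** A reader might infer that any protective main result would be spurious. Start dates are not given, and the windows at 0–12 and 13–27 weeks anticipate earlier use. If diabetes must be diagnosed (assumed weeks 24–30) before the event, the script follows within 1–4 weeks and 10–50% start early, null values for any script are 0.95–1.01 (all) and 0.86–1.00 (preterm). For two or more scripts the preterm values remain at 0.50–0.82.
- **Table S4 is not evidence of the bias.** It is tempting to read the weighted 0.56 for preterm preeclampsia as the artefact, but it rests on 4 exposed events. Preeclampsia overall is 0.98 crude and 0.96 weighted, outside the 0.68–0.89 simulated in step 2 for two or more scripts. The intervals are wide, and confounding by indication could push the other way.
- **The window from 28 weeks concerns use, not first use.** It can include women continuing from earlier, so a simulation of late starters does not measure it and no figure is given for it here. Preterm birth has the same structure but was not computed.

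**Conclusion.** The point holds as a fault in the stated analysis. An exposure that accrues during follow-up is treated as fixed at baseline, and the resulting bias runs below 1, whichever way women first dispensed after diagnosis are handled. It vanishes only if essentially all use starts early.

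Direction and ordering were the same in every scenario with starts after a gestational diabetes diagnosis: lower for preterm than for all preeclampsia, and lower for two or more scripts than for any. The size is less certain. A reasonable range for preterm preeclampsia with two or more scripts is about 0.3 to 0.8. For any script it runs from about 0.97–0.99 for all preeclampsia (starts within two weeks of diabetes diagnosis) to about 0.82–0.85, with preterm at about 0.56–0.63 at the late end. The most adverse patterns tried went lower still. All these figures rest on assumed start, diagnosis and script-interval timing, since the SAP gives none. Table S4 does not settle the matter either way.

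**What to change.** 1. Keep the rule that scripts after diagnosis do not count as exposure, and state how women first dispensed after diagnosis are handled.
2. For preeclampsia, its preterm strata and preterm birth, analyse metformin as time-varying on the gestational-age scale: unexposed until first dispensing, exposed after. Use weighted pooled logistic or Cox regression.
3. For script count and timing windows, use landmark analyses among women undelivered and free of preeclampsia at the landmark, with exposure fixed by dispensing before it. A 28-week landmark cannot capture use from 28 weeks onward; for that window use the time-varying model or a later landmark.
4. Where no diagnosis date is held and delivery date stands in, report this as a limitation, because scripts filled between diagnosis and delivery would be misclassified as prior exposure.

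Prescribing data are already linked and gestational age at exposure is already to be calculated, so no new data source is named as needed. The change does go beyond wording: the planned doubly robust estimator and its pooling over imputations must be specified again for the new models. Landmark intervals widen because earlier events are lost, and Table S4 has only 34 preterm cases (4 + 30). Women who start after a landmark count as unexposed, which dilutes any real effect and should be stated when those results are reported.

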**Null hypothesis**

Taking metformin during pregnancy does not affect the likelihood of developing preeclampsia among women with diabetes.

1. **Background**

Metformin is an oral hypoglycaemic agent prescribed to women in pregnancy with pre-existing Type II diabetes and gestational diabetes. It has well-described benefits for mother and neonate when used in this context [22]. Beyond diabetes, metformin has been reported to reduce the likelihood of pregnancy complications among women with polycystic ovary syndrome [23, 24], and in women with previous unsuccessful attempts at in vitro fertilisation (IVF) [25].

Compared with insulin, two meta-analyses concluded that metformin administration is associated with lower rates of preeclampsia[22], and pregnancy-induced hypertension [8]. However, in women with diabetes, studies in this area have been small. Population-based research with larger numbers could generate stronger evidence to better investigate this relationship.

The objective of this research is to determine the relationship between metformin and hypertensive disorders of pregnancy (preeclampsia, eclampsia, gestational hypertension) among women with diabetes, using a national population-based cohort from Scotland.

1. **Study population**

The population will include all nulliparous singleton pregnancies with a diagnosis of diabetes (gestational diabetes or Type II diabetes), recorded in the Scottish Morbidity Records between 2009 and 2018. The Scottish Morbidity Records hold data relating to pregnancy, delivery and perinatal outcomes for all women and infants discharged from maternity hospitals across Scotland.

Exclusion criteria:

a) Multifetal pregnancy

b) Parous women (to account for clustering)

c) Missing gestational age (which will be used to calculate gestational age at exposure)

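### The exposure-timing rule is tied to preeclampsia alone, so for gestational hypertension (O13), alone or within the hypertensive-disorders outcome, a script filled after onset still counts as exposure

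*SAP*

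**What the plan says.** The overview under Research question defines exposure without any cut-off: "I–Prescription of metformin during pregnancy". The Exposure section adds time windows, the last of them open-ended: "Metformin use will be further categorised as use ever, 0 – 12 weeks, 13 – 27 weeks, and 28 weeks onward". It then gives the only ordering rule in the document, on when scripts were filled: "with only prescription prior to preeclampsia diagnosis included".

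The outcomes are wider than that rule:

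- The overview names the outcome as "O–Hypertensive disorders of pregnancy".
- The objective, in the Background section, is stated for "hypertensive disorders of pregnancy (preeclampsia, eclampsia, gestational hypertension) among women with diabetes".
- The secondary outcomes begin with "Gestational hypertension ICD-O13", whereas the primary outcome, preeclampsia, is O11, O14 and O15.
- Table S1 builds hypertensive diseases of pregnancy from O13 together with O11, O14 and O15.

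The Outcome analysis section plans a separate model for each outcome but gives none of them its own exposure cut-off.

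**The concern.** An ordering rule exists so that a drug is not credited or charged with an event that came before it. Here it protects one outcome and is silent on the others. Take a woman recorded with gestational hypertension at 27 weeks who first fills metformin at 29 weeks and never develops preeclampsia. Under the plan as written she is an exposed woman with the event, although the event came first. For the composite there is a second group: women whose scripts fall between gestational hypertension and a later preeclampsia diagnosis. Those scripts pass the rule but come after the first hypertensive event.

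At stake is whether the results for gestational hypertension, and for the outcome named in the objective, can be read as metformin preceding hypertension.

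**Working it through.** **Inputs (Table S4, two or more scripts versus unexposed).** Group sizes are 637 and 2,672. Events are: hypertensive disorders 43 and 209; preeclampsia 18 and 77; pregnancy-induced hypertension 25 and 132.

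**Step 1: reproduce the printed crude risk ratios.** RR = (a/n1)/(b/n0), with SE of log RR = √(1/a − 1/n1 + 1/b − 1/n0).

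- Hypertensive disorders: (43/637)/(209/2,672) = 0.0675/0.0782 = 0.863. The SE is 0.162, giving a 95% CI of 0.63 to 1.18. The table prints 0.86 (0.63-1.18).
- Pregnancy-induced hypertension: the printed 4.0% and 5.1% require preeclampsia cases to be removed from the denominators, 637 − 18 = 619 and 2,672 − 77 = 2,595. Then (25/619)/(132/2,595) = 0.0404/0.0509 = 0.794. The SE is 0.213, giving a 95% CI of 0.52 to 1.21. The table prints 0.79 (0.52-1.21).

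**Step 2: can the rule reach these events?** 18 + 25 = 43 and 77 + 132 = 209. The two components add exactly to the composite, so they do not overlap: the 25 and 132 women are counted as having no preeclampsia. A rule keyed to the date of a preeclampsia diagnosis has no date to act on for them.

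**Step 3: share of the composite.** 25/43 = 58% of exposed events and 132/209 = 63% of unexposed events.

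**Step 4: what cannot be computed.** The document gives no count of scripts filled after O13 onset. Suppose, purely as an assumption, that 5 of the 25 exposed cases (20%) first filled metformin after onset.

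- Moving only those 5 to the unexposed group gives (20/614)/(137/2,600) = 0.62.
- If the same 20% of the 594 exposed non-cases (619 − 25 = 594; about 119) were also late starters and were moved as well, the result is (20/495)/(137/2,719) = 0.80, essentially the starting 0.79.

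The answer depends on how late starters are handled among women without the outcome, which the document does not let one determine. Neither figure is a corrected estimate.

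**The case against.** Several counter-arguments carry weight.

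*The rule fits the main question.* The research question, the null hypothesis and the primary outcome all concern preeclampsia. Gestational hypertension is secondary, and the composite, though it is the overview outcome and the objective, does not appear in the list of primary and secondary outcomes. This stands and limits the point to O13 and the O13 component of the composite. It does not remove it, because the plan still models those outcomes.

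*The bias runs towards harm.* A reader might infer this, since charging earlier events to metformin raises the risk ratio. Taken alone, that mechanism does. But in the same analysis women who remain pregnant and event-free have longer to fill a first script and be classed as exposed, which pushes the ratio down. The document does not support a net direction.

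*The risk ratio should really be about 0.62.* Moving a handful of exposed cases across gives such figures, but the number moved has no source and the calculation cuts exposure short in cases only. It shows what a lopsided rule produces, not the bias in this plan. It also perturbs the crude ratio, whereas the plan centres on doubly robust weighted estimates; Table S4 prints a weighted ratio of 0.96 for both outcomes.

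*Table S4 is not the main exposure.* This is correct. It covers women with two or more scripts, so the 58% and 63% describe that comparison and not necessarily the any-script analysis.

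*O13 dates may not exist.* Table S1 identifies disease by code, the records are described as relating to maternity discharges, and preeclampsia is stratified by gestational age at birth. The preeclampsia rule presupposes that diagnosis can be dated, but nothing confirms the same for O13. The fix has to allow for this.

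**Conclusion.** The point holds for gestational hypertension and for the O13 component of the hypertensive-disorders outcome. Followed as written, the plan counts scripts filled after the outcome as exposure, which is more than a missing detail. Where it can be seen, in Table S4, the component outside the rule is 25 of 43 exposed and 132 of 209 unexposed hypertensive events. That share rests on the table's own counts and on their exact additivity. The number of misordered scripts and the net direction of bias are unknown, so the point supports neither a claim of bias towards harm nor any replacement risk ratio. It also does not show that the primary preeclampsia analysis lacks an ordering rule. It is a change that should be made to the secondary and composite analyses.

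**What to change.** Define exposure separately for each hypertensive outcome, relative to the first record of that outcome: O13 for gestational hypertension, and the earliest of O11, O13, O14 or O15 for the composite. Then state how time before the first script is handled, identically for women with and without the outcome. There are two workable forms:

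1. **Time-varying exposure.** Pregnancy time and events before the first script count as unexposed. This uses all scripts up to the outcome, but it departs from the planned fixed binary exposure and logistic propensity model.
2. **A landmark at one of the plan's own window boundaries.** For example, define exposure through 27 weeks among women still pregnant and free of the outcome at 28 weeks. The planned IPWRA can still be fitted. Scripts from 28 weeks on are not counted, and events before the landmark leave the analysis.

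Do not simply add O13 to the existing sentence. A cut-off at diagnosis that applies only to women who have the outcome leaves the others with exposure time up to delivery, and so biases towards benefit.

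The cost is a short amendment, exposure re-derived per outcome from the linked scripts, and some extra analysis. It depends on usable O13 diagnosis dates; hypertension managed as an outpatient may be dated late, so some misordering could remain. If O13 dates are not available, say so and report the gestational hypertension and composite results as not time-ordered.

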| --- | --- | --- | --- | --- |
| **Age,** (years) | mean ±SD |  |  |  |
| **Age >35 years** | n (%) |  |  |  |
| **Body mass index** (kg/m^2^) | mean ± SD |  |  |  |
| **Body mass index >30mg/kg** | n (%) |  |  |  |
| **Ethnicity** | n (%) |  |  |  |
| **Smoking,** yes | n (%) |  |  |  |
| **Deprivation score**  1  2  3  4  5 | n (%) |  |  |  |
| **Pre-gestational disorders**  Hypertension  Cardiovascular disease  Autoimmune diseases  Diabetes  Type I  Type II  Renal disease | n (%) |  |  |  |
| **Year of birth**  2009  2010  2011  2012  2013  2014  2015  2016  2017  2018 | n (%) |  |  |  |
| **Gestational diabetes** | n (%) |  |  |  |

- 1. **Outcome analysis**

Potential estimators are (i) selection model, using inverse probability weighting (IPW); (ii) outcome model, using regression adjustment; (iii) doubly robust inverse probability weighted regression adjustment (IPWRA) models. Under correct specification, all the estimators should produce similar results. We will focus on IPWRA; selection model will be included in the IPW and outcome in regression (RA) model specification. We will combine both regression adjustment and augmented IPW in a doubly robust regression model. We will also perform RA, IPW and multivariate LR separately.

Model for exposure assignment using inverse probability weighted propensity scores derived from the logistic exposure model. Adequacy of balance achieved by PS weighting will be assessed using: (i) standardised mean difference for model covariates and variance estimates between exposure groups and (ii) propensity scores overlap. If unbalanced, we will explore measures such as: addition of interaction terms; different exposure models; use of alternate weighting structures (overlap or stabilized); and lastly propensity score-based trimming with the aim of achieving overlap if the propensity score distributions.

This will be performed for the overall cohort and then subgroup analyses will be performed.

The model will be created for each outcome with the final included covariates determined by the authorship team and informed by direct acyclic graphs (Fig S1, S2). Covariates to be considered:

1. Maternal age at delivery
2. Body mass index
3. Deprivation score
4. Ethnicity
5. Smoking status
6. Pre-existing maternal disease
7. Conception with assisted reproduction

All statistical analysis will be performed using StataSE version 17.0.

- 1. Handling of missing data

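### The SAP defines a 0–12 week metformin category but does not tie it to the two congenital anomaly outcomes, which by default fall under any use in pregnancy versus none

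*SAP*

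**What the plan says.** The overview of the main analysis (SAP, Research question) sets the contrast without a gestational window: "I–Prescription of metformin during pregnancy" against "C–No prescription of metformin during pregnancy". The study population is nulliparous singleton pregnancies with a "diagnosis of diabetes (gestational diabetes or Type II diabetes").

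The Exposure section adds timing categories: "Metformin use will be further categorised as use ever, 0 – 12 weeks, 13 – 27 weeks, and 28 weeks onward". It then gives one rule that links timing to an outcome, with "only prescription prior to preeclampsia diagnosis included".

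The secondary outcomes include "Major congenital abnormality (binary") and "Congenital renal anomaly (binary"). Neither entry names an exposure category or a comparator.

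The Outcome analysis section derives weights from a logistic exposure model, which points to a binary exposure. On outcomes it says: "The model will be created for each outcome with the final included covariates determined by the authorship team". It leaves covariates to be settled outcome by outcome but does not say which exposure category goes with which outcome.

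**The concern.** Structural anomalies arise early in pregnancy, so metformin first dispensed after that period cannot have caused them. Table S1 describes gestational diabetes as diagnosed during pregnancy, and the SAP expects most metformin to be prescribed for gestational or type II diabetes. Some women in the exposed group will therefore have started late. Under any use versus none, they are counted as exposed for an outcome already determined before their first prescription.

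The SAP accepts the principle behind this point for preeclampsia, where exposure must precede diagnosis. It does not carry the principle over to the anomaly outcomes.

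Two things are at stake. A risk ratio near 1 from the default contrast could be taken as reassurance about early exposure when it says little on that question. And with several exposure categories defined but none named as main for these outcomes, the choice can be made after the results are known.

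**Working it through.** The SAP states no anomaly rate, no distribution of start times and no power calculation, so there is no figure of its own to reproduce here. What follows is illustration under stated assumptions.

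**Inputs**
- Group sizes, from Table S4: 637 women with two or more metformin scripts and 2,672 unexposed. The 637 stands in for the ever-exposed group, whose size is not given.
- e, the share of exposed women with metformin at 0–12 weeks: not in the SAP; assumed 10% to 50%.
- R, the true early-exposure risk ratio: not in the SAP; assumed 1.5 to 3.
- Anomaly risk in the unexposed: not in the SAP; assumed 3% below (2% to 5% was also examined).

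**1. Dilution.** If late starters carry the unexposed risk p and there is no confounding, the risk among the ever-exposed is e·R·p + (1 − e)·p. Dividing by p gives RR_ever = 1 + e(R − 1).

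| R | e = 20% | e = 40% |
|---|---|---|
| 1.5 | 1 + 0.2 × 0.5 = 1.10 | 1 + 0.4 × 0.5 = 1.20 |
| 2.0 | 1 + 0.2 × 1.0 = 1.20 | 1 + 0.4 × 1.0 = 1.40 |

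**2. Power under the same assumptions.** Two-sided 5% level, unexposed risk 3%, R = 2.0, normal approximation for two proportions. The ever contrast uses 637 exposed, the early contrast e × 637; both use 2,672 unexposed.

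| e | RR, ever use | Power, ever use | RR, 0–12 weeks | Power, 0–12 weeks |
|---|---|---|---|---|
| 10% | 1.1 | 6% | 2.0 | 33% |
| 20% | 1.2 | 13% | 2.0 | 48% |
| 30% | 1.3 | 23% | 2.0 | 59% |
| 50% | 1.5 | 48% | 2.0 | 75% |

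The early contrast had more power in every scenario with e from 10% to 50%, risk from 2% to 5% and R from 1.5 to 3. The approximation is optimistic with so few events, so the ordering matters more than the levels.

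**3. Price in precision.** At e = 20% there are 0.2 × 637 ≈ 127 early-exposed women, with 127 × 6% ≈ 7.6 expected events. The unexposed have 2,672 × 3% ≈ 80.2 and the ever-exposed 637 × 3.6% ≈ 22.9.
- Early: SE(log RR) = √(1/7.6 − 1/127 + 1/80.2 − 1/2,672) ≈ 0.37, so a risk ratio of 2.0 would have a 95% interval of about 0.97 to 4.11.
- Ever: SE = √(1/22.9 − 1/637 + 1/80.2 − 1/2,672) ≈ 0.23, so a risk ratio of 1.2 would have about 0.76 to 1.89.

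**4. Confounding in the other direction.** Suppose metformin has no effect, anomaly risk in type II diabetes is twice that in gestational diabetes, and type II makes up 30% of exposed and 5% of unexposed women (all assumed).
- Crude ever-use RR = (0.70 × 1 + 0.30 × 2)/(0.95 × 1 + 0.05 × 2) = 1.30/1.05 = 1.24.
- If every early user has type II diabetes, crude early-use RR = 2.0/1.05 = 1.90.

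So diabetes type can raise either estimate, and the early contrast is the more exposed to it. Changing the window without handling diabetes type would exchange one bias for another.

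**The case against.** The timing categories stand in the general Exposure section, ahead of every outcome list, and are not limited to preeclampsia. On a natural reading each outcome, anomalies included, would also be examined by window, so a 0–12 week anomaly result may already be intended. The models are built outcome by outcome with covariates guided by causal graphs that are not shown, so how those graphs treat anomalies or diabetes type cannot be judged. The anomalies are secondary outcomes in a study whose question and null hypothesis concern preeclampsia, and the SAP makes no safety claim from them. The dilution figures rest on assumed inputs.

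Much of this stands. A reader might infer that the SAP analyses anomalies only against use at any time; it does not say so. A reader might also infer that the ever-use estimate must be biased towards 1. That needs late starters to carry the unexposed risk and no confounding by diabetes type, and the SAP establishes neither.

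What does not fall is the gap itself. Listing a category does not make it the main exposure for an outcome, and the SAP does not state the comparator for the 0–12 week group: never-users only, or later starters as well. The contrast it does name as main is the one least suited to outcomes determined early.

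**Conclusion.** The point holds as a gap in specification. By default both anomaly outcomes fall under any use versus none; the first-trimester category exists but is not assigned to them. If that default is reported as the main result, and if late starters carry the unexposed risk without confounding, a true early risk ratio of 2.0 would show as 1.2 to 1.4 when 20% to 40% of exposed women were treated by 12 weeks. The actual size cannot be worked out from the SAP, which gives neither start times nor anomaly counts, and the net direction is open because diabetes type may act the other way. As these are secondary outcomes, the study's main question is untouched, but the change is worth making before analysis.

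**What to change.** For major congenital abnormality and congenital renal anomaly, state in the SAP that:
- the main exposure contrast is metformin dispensed at 0–12 weeks versus no metformin in pregnancy;
- women who started only after 12 weeks are shown as a separate group, neither exposed nor reference;
- ever use is a supplementary analysis;
- diabetes type (type II versus gestational) enters the propensity and outcome models by name. The covariate list has pre-existing maternal disease, which may or may not cover it. Overlap is then checked as the Outcome analysis section already requires.

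The window is already planned, so no new data are needed. The cost is a separate propensity model with its own balance checks, fewer exposed women and a wider interval. Overlap may also be limited if early use occurs almost only in type II diabetes; if so, that should be reported as a limit on what the data can say about early exposure.
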